**Fig. 1 Fig1:**
[figure not shown]
SPIRIT diagram

The primary outcome will be the participants’ PA measurement assessed at baseline and at 6 months using the IPAQ-SF. Secondary outcomes will include changes in participants’ frailty status, biometric measurements, quality of life, and biopsychosocial assessments at baseline and at 6 months (Table 1).

**Table 1 Tab1:** Data measurements to be recorded during the study period

	Baseline	Study period	6 month follow-up
**Self-reported**	IPAQ-SF		IPAQ-SF
	IMSA		IMSA
	SF-12		SF-12
**Healthcare professional reported**	Vivifail questionnaire		Vivifail questionnaire
	BMI		BMI
	Abdominal perimeter		Abdominal perimeter
	Calf perimeter		Calf perimeter
**Sensor data**		Number of steps	
		Heart rate	
		Sleep quality	
**EHR data**	Historical clinical data	Unplanned hospital admissions	

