**Methods:**

This study aims to measure the effects of behavioral change techniques (BCTs) delivered by a wearable device on physical activity and quality of sleep (QS) in older adult patients with MM. We designed an open-label randomized controlled trial with participants recruited through primary care and a specialist outpatient clinic. Participants must be more than 65 years old, have MM, and have access to smartphones. All eligible participants will receive PA promotion content and will be randomly assigned to wear a smartwatch. The primary outcome will be the participants’ PA measurement at baseline and at six months using the International Physical Activity Questionnaire - Short Form (IPAQ-SF). Secondary outcomes will include changes in the participants’ frailty status, biometric measurements, quality of life, and biopsychosocial assessments. A sample size of 40 participants per arm was calculated to detect group differences, with 50 participants planned to recruit and randomize into each arm.

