### Inclusion and exclusion criteria

Patients may be included if they are more than 65 years old and have MM. We will use a previously proposed definition of MM as the presence of two or more of the following chronic conditions: hypertension, depression or anxiety, chronic musculoskeletal conditions causing pain or limitation, arthritis and/or rheumatoid arthritis, osteoporosis, asthma, chronic obstructive pulmonary disease (COPD), ischemic heart disease, peripheral artery disease, heart failure, cerebrovascular diseases, chronic stomach or colon conditions, chronic hepatitis, diabetes mellitus, thyroid disorders, any active cancer in the previous five years, chronic kidney disease, chronic urinary conditions, hyperlipidemia, and obesity [22]. In addition, participants must have access to their smartphones. Exclusion criteria will include: patients who are sufficiently physically active, defined with International Physical Activity Questionnaire - Short Form (IPAQ-SF) > 150 min aerobic physical activity per week, an existing absolute contraindication for PA according to the American College of Sports Medicine (acute myocardial infarction within two days, ongoing unstable angina, uncontrolled cardiac arrhythmia with hemodynamic compromise, active endocarditis, symptomatic severe aortic stenosis, decompensated heart failure, acute pulmonary embolism, pulmonary infarction, deep venous thrombosis, acute myocarditis or pericarditis, acute aortic dissection, physical disability that precludes safe and adequate testing), poor comprehension of Portuguese language, disabling neurological disorder (defined as mRankin score $$\ge$$ 4), severe psychiatric illness, learning disability, dementia and cognitive impairment, registered blind, housebound or resident in a nursing home, non-ambulant, advanced cancer, and scheduled for surgery within five months after the first consultation. Orthopedic or rheumatologic diseases with severe impairment and chronic pain syndromes with inherently reduced mobility will also not be included.

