### Statistical analysis

A sample size of 40 participants per arm was calculated to be sufficient to detect a group difference, with the alpha set at 0.05, and the power set at 0.80. Protecting against a dropout rate of 20% over the 6-month study duration, 50 participants will be recruited and randomized into each arm (A or B). We will conduct an exploratory analysis of the recorded data. This will be based on descriptive statistics and will be used to characterize the universe of data and identify outliers and general trends. Agreement between IPAQ-SF and wearable activity will be assessed trough Cohen’s kappa. We will use McNemar’s test to compare groups at baseline and 6-month follow-up regarding the study outcomes. In addition, we will assess the impact of wearable data and PROMs in predicting unplanned hospital admissions using classification accuracy, absolute error, and ROC AUC analysis.

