## Discussion

We will employ the IPAQ-SF to measure the level of activity in all patients and therefore detect differences between patients who will be using wearables and those who will not. Despite conflicting evidence regarding the correlation with objectively measured PA, this test is highly reported in the literature and has been previously validated in Portuguese. We expect that the results of this study will contribute to better knowledge about the PA patterns of patients with MM as well as the impact of PA intervention in this population, a topic that is underexplored in the literature [16].

In addition, we aim to explore the influence of different PA patterns on other important outcomes such as PROMs and healthcare resource utilization. For this purpose, we will make use of a PROMs registry that has been developed locally for the purpose of data entry. We aim to understand the added impact of wearable data on medical information data for predicting PROMs and unplanned hospital admissions. Data from participants’ medical records will be assessed in the following fields: previous diagnosis, previous hospital episode types and specialties, previous medical procedures, biometrics (weight, height, and BMI), clinical notes, laboratory results, and drugs prescribed or administered in an inpatient setting. The recorded data will be anonymized and stored locally. We aim to understand whether there is any added impact of using this information for future modeling.

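### The primary outcome names a questionnaire and two visits but no between-arm contrast, and the one test named for the outcomes (McNemar's) does not supply one, so the stated alpha and power attach to no identified comparison.

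*Protocol article*

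**What the plan says.** Study measures and outcomes defines the primary outcome as "PA measurement assessed at baseline and at 6 months using the IPAQ-SF". The Methods paragraph of the Abstract says the same and adds no score or contrast.

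The Statistical analysis section sizes the trial at 40 per arm, "sufficient to detect a group difference, with the alpha set at 0.05, and the power set at 0.80". It gives no effect size, SD or proportions. For the outcomes it names one test, McNemar's, to be used "to compare groups at baseline and 6-month follow-up regarding the study outcomes".

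Elsewhere the IPAQ-SF appears in other roles:
- In the eligibility criteria it is weekly minutes with a cut, "> 150 min aerobic physical activity per week".
- In the agreement analysis with the wearable it must be a category, because Cohen's kappa is used. The categories are not given.
- In the Discussion it serves "to measure the level of activity in all patients and therefore detect differences between patients" with and without wearables. This is the clearest statement that a between-arm comparison is intended.

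**The concern.** A confirmatory claim needs three things to fit together: a variable, a contrast between the randomised arms, and a test of that contrast. Here the variable is open (minutes, a category, or a yes/no split). The contrast is open (6-month value, change, or baseline-adjusted difference). The test that is named answers a different question.

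McNemar's test compares two paired binary readings, such as the same participants before and after. Arms A and B are independent groups randomised 1:1, so there is no pairing between them. Followed literally, the plan would show whether participants within a group changed. Both arms receive activity promotion, so a change within Arm A is not evidence for the devices.

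The trial is open-label and its primary outcome is self-reported, so it matters that the deciding comparison is fixed before anyone sees the data.

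**Working it through.** **Inputs from the protocol article.** 40 evaluable per arm, alpha 0.05, power 0.80, 20% dropout and 50 randomised per arm (Statistical analysis); 1:1 allocation (Study intervention).

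**Assumed, because the article gives no figures.** Two-sided testing; unit SD; correlation r between baseline and 6 months of 0.3 to 0.7, with 0 as a limiting case; normal data unless stated otherwise.

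**1. The plan's own figures.** Dropout: 40/(1 − 0.20) = 50, which reproduces. The 40 per arm can be neither reproduced nor refuted without an effect size. It can only be solved backwards:
- Continuous: d = (1.960 + 0.842) × √(2/40) = 2.802 × 0.2236 = 0.626 (0.634 with the t distribution), so about 0.63 SD. One-sided it would be 0.56.
- Binary, no continuity correction: for example 10% vs 36%, 20% vs 50%, 30% vs 61%, or 50% vs 80%.

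These are different trials, and the article does not say which was meant.

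**2. Power by contrast for the same true difference (d = 0.626, 40 per arm).** Power = Φ(d/(s√(2/40)) − 1.960) = Φ(2.802/s − 1.960). Here s = 1 for the 6-month value, √(2(1 − r)) for change, and √(1 − r²) for the baseline-adjusted difference.

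| r | 6-month value | change | baseline-adjusted |
|---|---|---|---|
| 0 | 0.80 | 0.51 | 0.80 |
| 0.3 | 0.80 | 0.66 | 0.84 |
| 0.5 | 0.80 | 0.80 | 0.90 |
| 0.7 | 0.80 | 0.95 | 0.98 |

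Example, adjusted at r = 0.5: s = √0.75 = 0.866; 2.802/0.866 − 1.960 = 1.275; Φ = 0.90.

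Dichotomised at 6 months, with the cut c SDs above the control mean, the proportions are 1 − Φ(c) and 1 − Φ(c − d):
- c = 0: 0.500 vs 0.734, power 0.58
- c = 0.5: 0.309 vs 0.550, power 0.59
- c = 1: 0.159 vs 0.354, power 0.52

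With d = 0.634 and a pooled-variance formula, 0.50 vs 0.737 gives about 0.59 and 0.375 vs 0.625 about 0.61. The range is therefore about 52–61%.

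**3. What McNemar's test would show.** In 20,000 simulated trials per correlation there was no device effect, both arms improved by an assumed 0.5 SD, and the score was split at the baseline mean. McNemar's test within Arm A was significant in 39%, 45% and 54% of trials at r = 0.3, 0.5 and 0.7.

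Suppose instead that the split were the 150-minute eligibility cut (an assumption). Everyone enrolled starts on the inactive side, so movement can go only one way. The exact two-sided p-value is then 2 × 0.5^k for k participants who cross: 0.0625 for k = 5 and 0.031 for k = 6. Six crossers in an arm make the test significant, whatever happens in the other arm.

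**4. False positives with no effect.** Each continuous between-arm contrast, fixed in advance, rejected in 4.9–5.1% of these simulated trials (the uncorrected test of proportions in 5.5–5.8%). At least one of four (6-month value, change, baseline-adjusted, dichotomised) was significant in 12.0%, 12.4% and 12.9% at r = 0.3, 0.5 and 0.7. A second model used skewed minutes with many zeros and baseline at most 150 (4,000 trials per correlation). It gave 7.9–9.2% for three readings and 10.2–11.0% for six. Some of those readings used an energy-weighted score that the article does not mention.

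**The case against.** The strongest reply is scope. This is a condensed article, and scoring rules and model details usually sit in a full protocol or analysis plan. That stands for covariates, missing data and scoring. It does not dispose of the point, because the article does state a primary outcome, an alpha, a power and a test, and these do not fit together or match the comparison that the Discussion intends.

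It is also fair that the IPAQ-SF roles listed above are not rival primary outcomes. The 150-minute cut is an eligibility rule, kappa belongs to an agreement analysis, and the Discussion's phrase is ordinary prose. They show only that no place in the article settles the variable.

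A reader might infer four stronger things that the article does not support:
- **That there is no hierarchy of outcomes.** There is: the IPAQ-SF is primary and the others are labelled secondary. The 0.05 appears only in the sample-size sentence, not as one alpha shared by all outcomes.
- **That a between-arm test at baseline is planned.** The sentence can be read that way. With a paired test it can equally mean baseline against 6 months.
- **That 80% power can hold for only one form of the outcome.** Step 2 contradicts this: change reaches 80% at r = 0.5, and the adjusted contrast exceeds it at every r from 0.3 to 0.7.
- **That the true type I error is about double.** This requires choosing after seeing the data, which the article does not say will happen. The size also depends on an assumed list of readings.

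**Conclusion.** The point holds in this form: the article identifies no primary variable and no primary between-arm contrast, and the test it names cannot provide one. The 0.05 and the 0.80 are therefore not properties of any stated comparison. This should be put right before analysis.

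On assumed inputs (two-sided test, normal scores, r from 0.3 to 0.7), a true difference of about 0.63 SD would be detected with power of about 84–98% by a baseline-adjusted comparison and about 52–61% by a dichotomised one. The eligibility rule restricts the baseline range, so r may lie towards the low end; even at r = 0 the adjusted contrast keeps about 80%. The 8–13% false-positive range applies only if the contrast is chosen after the data are seen, and is indicative only. A single contrast fixed in advance keeps 5%.

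**What to change.** In Study measures and outcomes, and again in Statistical analysis, name one primary contrast: the difference between Arm A and Arm B in total IPAQ-SF minutes per week at 6 months, in the unit already used for eligibility. Analyse it with one pre-chosen linear model adjusted for baseline IPAQ-SF minutes, for example on the minutes scale with robust standard errors because of skew, two-sided 0.05, in place of McNemar's test. Choose the scale now: a log scale and a minutes scale estimate different quantities and can disagree, so listing both would leave the choice open.

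Use baseline only as a covariate, and treat other IPAQ-SF forms as supportive. The existing primary/secondary labels can stay.

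Restate the sample size as a difference in minutes with its SD. 40 per arm gives 80% power for about 0.63 SD before adjustment, two-sided. The sponsor must supply the SD.

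The cost is a few sentences, with no added data, visits or participants. The downside is that a favourable result on another IPAQ-SF form could not then be claimed as the primary result.

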### Statistical analysis

A sample size of 40 participants per arm was calculated to be sufficient to detect a group difference, with the alpha set at 0.05, and the power set at 0.80. Protecting against a dropout rate of 20% over the 6-month study duration, 50 participants will be recruited and randomized into each arm (A or B). We will conduct an exploratory analysis of the recorded data. This will be based on descriptive statistics and will be used to characterize the universe of data and identify outliers and general trends. Agreement between IPAQ-SF and wearable activity will be assessed trough Cohen’s kappa. We will use McNemar’s test to compare groups at baseline and 6-month follow-up regarding the study outcomes. In addition, we will assess the impact of wearable data and PROMs in predicting unplanned hospital admissions using classification accuracy, absolute error, and ROC AUC analysis.

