### Study intervention

All Participants who are eligible and consented to participate in the study shall receive PA promotion content in accordance to the Swedish model [23]. This method consists of five core components: (1) person-centered health promotion consultation; (2) a written prescription of physical activity; (3) a prescription guided by evidence-based knowledge on physical activity in the prevention and treatment of health conditions; (4) a follow-up of the written prescription; and (5) collaboration between the healthcare service and physical activity organizers outside healthcare. It is also emphasized that the method should be tailored to the local conditions in healthcare organizations. More specifically, we will recommend PA and provide informative flyers according to the Portuguese National Healthcare Authority and the World Health Organization recommendations for older age people. In addition to PA promotion counseling, all patients will be randomly allocated to either the intervention or the control groups using block randomization generated by a computer-generated random number sequence^1^. The allocation sequence will be generated by a research assistant who will not be involved in the data collection process. Eligible participants will be randomly assigned in a 1:1 ratio to one of the following intervention arms: Arm A (experimental arm), use of the device activity watch (Fitbit Sense), and a sleep monitoring mattress (Withings SA, France - Sleep Analyzer); Arm B (control): non-use of the devices. Participants randomized to wearable device BCT (Arm A) will be provided goal setting, self-monitoring and feedback. On the first visit they will undergo a brief training session where they’ll learn how to effectively use both devices, sync their data, and interpret the feedback they receive. Arm A participants will receive weekly feedback based on their activity and sleep data trough their devices. This might include suggestions for increasing step counts or tips for better sleep hygiene. The study team will provide a communication channel available for participants to address any technical issues or queries they might have regarding device usage. They will be instructed to wear the wearable device all the time (except when charging) and use the mattress while sleeping. Patients who do not use the device for at least 60% of the time will be excluded from the trial. Compliance of divide use will be regularly monitored by the study team.

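### The 80% power is claimed for a difference between arms, but the only comparison test named is McNemar's, which cannot compare independent arms

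*Protocol article*

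**What the plan says.** The Statistical analysis section of the protocol article states "A sample size of 40 participants per arm was calculated to be sufficient to detect a group difference, with the alpha set at 0.05", with "the power set at 0.80". It then raises 40 to 50 per arm to allow for 20% dropout over six months. The Abstract repeats the claim: "A sample size of 40 participants per arm was calculated to detect group differences". Under Study intervention, "Eligible participants will be randomly assigned in a 1:1 ratio" to the devices or to no devices, and both arms receive the same activity promotion. The Discussion gives the purpose of the IPAQ-SF as finding differences between those who use wearables and those who do not.

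The Statistical analysis section names one test for comparing groups on the study outcomes at baseline and six months: McNemar's. The primary outcome is physical activity by IPAQ-SF at those two visits. The article does not say whether it is analysed as minutes, a score or a category. The eligibility criteria exclude anyone above 150 minutes per week on the IPAQ-SF.

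Study intervention also says "Patients who do not use the device for at least 60% of the time will be excluded from the trial".

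**The concern.** Power belongs to a particular test of a particular difference. Here the claim is about "sufficient to detect a group difference" with a number per arm, which describes two independent samples. McNemar's test takes pairs of yes/no results and uses only the pairs that change. Applied to baseline and six months, it asks whether one set of people changed. It does not ask whether the device arm changed more than the control arm.

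Two things are at stake. First, the reader is given 0.80 for an analysis that the article does not describe. Second, if McNemar's test is run within each arm, a change in Arm A could be credited to the device although counselling alone, which both arms receive, would produce it. The wear rule adds a further problem. Arm B has no device, so the rule can remove only Arm A patients, after randomisation and on the basis of their behaviour.

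**Working it through.** **Inputs from the article:** 40 analysable per arm, alpha 0.05, power 0.80, 1:1 allocation, 20% dropout, McNemar's test, entry cap of 150 min/week. **Not stated there:** effect size, SD or rates, sidedness, outcome scale, expected proportion below 60% wear. Values marked as assumed below are mine.

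**1. The plan's own figure.** 40 / (1 − 0.20) = 50 per arm. This reproduces. The 40 cannot be reproduced forwards, because no effect size is given.

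**2. Does 40 follow from McNemar's test?** Let p10 and p01 be the proportions changing in each direction, s = p10 + p01 and d = p10 − p01. Pairs needed = (1.960·√s + 0.842·√(s − d²))² / d².

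| Assumed p10 / p01 | Pairs needed |
|---|---|
| 0.30 / 0.10 | 77 |
| 0.20 / 0.05 | 85 |
| 0.30 / 0.05 | 42 |
| 0.35 / 0.05 | 33 |

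For the first row: (1.960·√0.40 + 0.842·√0.36)² / 0.04 = (1.240 + 0.505)² / 0.04 ≈ 76.1, rounded up to 77. Some inputs give a number near 40, but it would be a number of pairs in one group, not a size per arm for a group difference.

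**3. What McNemar's test could show in controls alone.** Assume the binary outcome is exceeding 150 min/week. By eligibility nobody exceeds it at baseline, so every change is upward. With k changes all in one direction, the exact two-sided p-value is 2·0.5^k: 0.0625 for k = 5 and 0.031 for k = 6. The test therefore rejects when at least 6 of 40 become active. From the binomial distribution with n = 40:

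| Assumed proportion of controls active at 6 months | Probability of rejection |
|---|---|
| 10% | 0.21 |
| 15% | 0.57 |
| 20% | 0.84 |

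None of these involves a device effect.

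**4. What 40 per arm can detect between arms** (two-sided 0.05, power 0.80, continuous outcome). Normal approximation: (1.960 + 0.842)·√(2/40) = 0.626 SD; by t-test, 0.634 SD. Baseline adjustment multiplies this by √(1 − r²), with r the assumed correlation between baseline and six months:

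- r = 0.5: 0.634 × 0.866 = 0.55 SD
- r = 0.7: 0.634 × 0.714 = 0.45 SD

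Unadjusted t-test power at 40 per arm is 60% at 0.5 SD, 42% at 0.4 SD and 26% at 0.3 SD.

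**5. Wear-time removals.** Assume a further 20% of Arm A's 40 completers are removed: 40 × 0.80 = 32, against 40 in Arm B. The standard error is √(1/32 + 1/40) = 0.237 SD. Power at 0.626 SD = Φ(0.626/0.237 − 1.960) = 0.75, against 0.80 with 40 and 40. If 10% or 30% are removed (36 or 28), power is 0.78 or 0.72. If the 20% dropout allowance already covers these removals, there is no loss.

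**The case against.** The strongest reply is that this is a journal article. The effect size and its derivation may stand in the full protocol, and the one calculation that can be checked, 40 to 50, is right. That stands as far as the missing effect size goes: its absence from the article is not the point made here. It does not answer the mismatch. An effect size printed elsewhere would still belong to a two-arm comparison, while the article names a paired test for comparing groups. If another document names a between-arm test, the article states the analysis wrongly.

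Four stronger readings are tempting, and the documents do not support them.

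- A reader might infer that 80% power holds only from 0.63 SD upwards. That figure assumes a two-sided, unadjusted comparison on a continuous scale, none of which the article fixes. One-sided, it is about 0.56 SD; with baseline adjustment, 0.55 or 0.45 SD at the assumed correlations.
- A reader might infer that moderate effects are more likely to be missed than found. At 0.5 SD the unadjusted power is 60%, and with baseline adjustment at r = 0.5 about 72%, so that statement should not be made.
- A reader might infer that the wear rule breaks the power calculation. No removal rate is given, and the 20% may include these patients. Even with 32 against 40, a baseline-adjusted analysis at r = 0.5 has about 86% power at 0.634 SD. The main objection to the rule is selective removal from one arm, not lost numbers.
- A reader might infer that a large effect is implausible because both arms are counselled. The article gives no expected effect, and Arm A also receives goal setting, self-monitoring and weekly feedback, so this remains opinion.

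Exclusion from the trial might also be meant as withdrawal from the intervention rather than from the analysis. The article does not say so, and the wording invites removal.

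**Conclusion.** The point holds as a mismatch between the power claim and the named test. It needs no figure from outside the article: McNemar's test cannot compare two independent randomised arms, so the stated 0.80 is not the power of the stated analysis. It is not an arithmetic error.

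The false-attribution figures, 0.57 and 0.84, rest on two assumptions: that the outcome is the 150 min/week threshold, and that 15% or 20% of controls become active. The detectable differences are back-calculated and are not the sponsor's design values. The entry cap narrows the baseline range and may lower r, so 0.55 and 0.45 SD could be optimistic. The power loss from wear-time removals is conditional and modest. That the rule acts on one arm only follows directly from the design.

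**What to change.** Keep 50 per arm, and make three changes.

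1. **Test.** Replace McNemar's test for the primary outcome with a between-arm comparison of 6-month IPAQ-SF adjusted for the baseline value (ANCOVA), on a stated continuous scale. Interpret the result from the estimate and its 95% confidence interval.
2. **Power statement.** State the effect size, sidedness and test actually used to reach 40, and show that they belong to this analysis. If no effect size was used, write: with 40 evaluable per arm and two-sided alpha 0.05, the trial has 80% power for a between-arm difference of about 0.63 SD unadjusted, or about 0.55 SD (assumed r = 0.5) to 0.45 SD (assumed r = 0.7) after baseline adjustment.
3. **Population.** Analyse all randomised participants as allocated, and remove nobody from the primary analysis for wear below 60%. Wear time may be used in a sensitivity analysis. If the removal is kept, state whether the 20% allowance covers it.

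No extra patients are needed, but this is more than rewording: the named test and the analysed population change. Stating the detectable difference also makes the power look less favourable for moderate effects.

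### Cohen's kappa is the only planned measure of agreement between IPAQ-SF and the watch; alone it cannot show how far, or in which direction, self-report departs from measured activity

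*Protocol article*

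**What the plan says.** The Statistical analysis section of the protocol article fixes one agreement statistic: "Agreement between IPAQ-SF and wearable activity will be assessed trough Cohen’s kappa".

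The two measures are described as follows.

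- **IPAQ-SF.** It is the primary outcome: "The primary outcome will be the participants’ PA measurement assessed at baseline and at 6 months using the IPAQ-SF" (Study measures and outcomes). The one scale the article gives for it is minutes per week, in the exclusion rule "Short Form (IPAQ-SF) > 150 min aerobic physical activity per week" (Inclusion and exclusion criteria).
- **Watch.** Table 1 lists "Number of steps", heart rate and sleep quality as sensor data, all in the study-period column and none at baseline.
- **Who has a watch.** Arm A has "use of the device activity watch (Fitbit Sense), and a sleep monitoring mattress"; the other arm is "Arm B (control): non-use of the devices" (Study intervention). For Arm A, "On the first visit they will undergo a brief training session", so the device is introduced at the baseline visit.

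The Discussion introduces the IPAQ-SF with the words "Despite conflicting evidence regarding the correlation with objectively measured PA".

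**The concern.** Kappa compares two classifications. To use it here, minutes per week and steps must both be cut into the same categories. After the cut, a small and a large disagreement across the same boundary count alike, and disagreement within a category disappears. The value obtained also reflects where the boundaries were placed.

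This matters because the primary outcome is self-reported in an open-label trial, and the article concedes doubt about how it relates to objective activity. The agreement analysis is the only check on that outcome that the article describes. A reader of the results would want to know whether participants over- or under-report, and by how much. Kappa does not estimate either.

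**Working it through.** **1. How many people can contribute.** The plan's own inflation reproduces: 40/(1 − 0.20) = 50 per arm. Arm B has no device, and Arm A has no device data before the baseline questionnaire. The only IPAQ-SF with a wearable counterpart is therefore the 6-month one in Arm A: at most 50 people, and 50 × 0.80 = 40 after the planned dropout. These people have received feedback from the device that serves as the comparator, and the article removes those who wear it less than 60% of the time.

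**2. Dependence on cut-points.** The article gives no correlation between the measures, so a range is assumed: latent bivariate normal with correlation ρ of 0.3, 0.5 or 0.7. For two binary cuts with upper fractions p1 and p2, and a = P(both above):

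- observed agreement po = 1 − (p1 − a) − (p2 − a)
- chance agreement pe = p1·p2 + (1 − p1)(1 − p2)
- κ = (po − pe)/(1 − pe)

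For both cuts at the median this reduces to κ = 2·arcsin(ρ)/π, which gives 1/3 at ρ = 0.5 and confirms that entry of the table.

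| ρ | both at 50% | both at 30% | both at 10% | tertiles, unweighted | one at 50%, other at 20% |
|---|---|---|---|---|---|
| 0.3 | 0.194 | 0.182 | 0.129 | 0.131 | 0.135 |
| 0.5 | 0.333 | 0.318 | 0.249 | 0.237 | 0.226 |
| 0.7 | 0.494 | 0.479 | 0.409 | 0.377 | 0.317 |

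The underlying association is the same along each row; only the categories change.

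**3. Blindness to bias.** In the row for ρ = 0.5, the last column describes a systematic shift: one measure puts 50% in the upper category and the other 20%. It gives 0.23. The tertile and 10% columns contain no shift and give 0.24 and 0.25. A kappa of that size therefore cannot tell a shift from random scatter. If each measure is instead cut at its own quantiles, adding a constant to everyone's self-report leaves kappa unchanged.

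**4. Precision.** Take an assumed κ of 0.40 with 50% margins, so that po = 0.70 and pe = 0.50. At n = 40, SE = √(0.70 × 0.30/40)/0.50 = 0.145, and the 95% interval is 0.40 ± 0.284, or 0.12 to 0.68. With equal margins of 30% and 15%, the large-sample half-widths are 0.31 and 0.39. At n = 50 the three half-widths are 0.25, 0.28 and 0.35. For assumed κ of 0.2 and 0.6 at n = 40, they run from 0.30 to 0.38 and from 0.25 to 0.35.

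A correlation is not precise at this size either. For r = 0.5 and n = 40, Fisher's transformation gives 0.549 ± 1.96/√37 = 0.549 ± 0.322, or 0.22 to 0.70. The case for a continuous measure is therefore what it estimates, not a large gain in precision.

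**The case against.** The strongest reply is that kappa is a standard statistic for two classifications on a common scale. The article already classifies the IPAQ-SF at a minutes-per-week threshold and plans McNemar's test, so a categorical reading of activity is consistent with the rest of the plan. Cut-points, weighting and time window are details that an article may leave to a fuller document that is not shown. All of this stands: kappa is not an error, and the missing cut-points are not counted here.

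A second reply is that the replacement has the same difficulty. Steps and minutes have different units, and Table 1 lists no active minutes, so limits of agreement cannot be computed from the listed variables. This also stands. It makes Bland-Altman conditional on a further variable, but it does not touch rank correlation, which needs no common unit.

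A third reply is that the margins of the two-by-two table would show which measure classifies more people as active. That is true if the cuts share one meaning, but it gives a direction at one threshold and no size in minutes.

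A reader might also infer that the restriction to Arm A after baseline counts against kappa. It does not: it limits every agreement statistic equally, including those proposed here. It is a reason to state the population, and nothing in the article claims agreement for Arm B or at baseline.

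**Conclusion.** The point holds as a limitation of using kappa alone. It is an admissible statistic, but as the only one it discards information that is collected, varies with the categories (0.23 to 0.33 at an assumed correlation of 0.5) and leaves any reporting bias in the primary outcome unestimated. The correlations, kappa values and margins used above are assumptions; the numbers of people are the article's.

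Two stronger readings are not supported. One is that kappa is the wrong measure and must be dropped; with common categories it is valid. The other is that kappa will be depressed because nearly everyone falls in one category. The exclusion rule puts everyone on one side of 150 minutes at baseline, but the usable comparison is at 6 months, after activity promotion and device feedback, and the article gives no distribution for that time.

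Severity is minor. Agreement is listed as neither a primary nor a secondary outcome, and the comparison between arms does not depend on it.

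**What to change.** Amend the agreement sentence in the Statistical analysis section as follows:

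1. In Arm A at the 6-month visit, report the Spearman correlation between IPAQ-SF minutes and step counts over the days the questionnaire refers to. This uses variables already listed, but it measures association and does not estimate bias.
2. If active minutes can be exported or derived from the watch, add the Bland-Altman mean difference and limits of agreement in minutes per week. This is the part that estimates over- or under-reporting.
3. Keep kappa as a secondary view, weighted if there are more than two ordered categories.
4. State that the result applies only to Arm A device users at follow-up (at most 50, about 40 after dropout), who have seen the device feedback, and that it is not carried over to Arm B.

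The cost is a little more exploratory analysis and possibly one more device variable to export. No visit, sample size or primary analysis changes.
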